### Honorarium

A £10 voucher for a local store that cannot be used to buy alcohol, will be given after completion of preliminary screening, on each of the 2 days of completion of the CANTAB testing plus a further voucher on completion of the follow-up contacts.

### Sample size

As this is a Proof of Concept study, previous data on the target population was not available. However, previously published studies using the CANTAB test battery in depressed patients have shown effect sizes of 0.5, 0.8, 0.76 [48], 0.496, 0.5 [51], 0.897 [49] and, 0.7 for spatial working memory in the elderly [50]. Similar values were obtained studying effects of acute alcohol withdrawal using an early version of the CANTAB [52]. We estimated the numbers needed in each group for a variety of effect size estimates based on a power of 80 % and alpha of 0.05. For an effect size difference of 0.8 25 subjects per group would be required and this increased to 32 for an effect size difference of 0.7 and 63 if the difference was 0.5. As a proof of principle study we erred on the side of caution and aimed to detect a small to medium effect size of 0.5 and this required 120 subjects participating in the study.

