### Assessment of safety

The procedures involved in this research are unlikely to cause significant discomfort or distress to participants. All questionnaire measures and research procedures have been widely validated and used in previous research without causing any problems to participants. Mifepristone has a good safety record and has been used clinically for over 15 years for other applications. However should any distress or discomfort occur with any of the procedures trained medical and nursing staff will be available on a 24 h basis to provide help and support. All staff involved in the care of trial participants will receive training on the conduct of the trial protocol. In particular training will be provided on the detection and management of expected and unexpected adverse drug events.

The collection and reporting of Adverse Events will start following the first dose of the trial medication and will continue until the last dose of the trial medication. Reporting of Serious Adverse Events, Serious Adverse Reactions and Suspected Unexpected Serious Adverse Reactions will continue until 14 days after stopping the trial medication. All concomitant medications will be recorded until 14 days after stopping the trial medication.

Daily assessments by the clinical team to monitor for signs of nausea or fatigue that might indicate adrenal insufficiency will be made. Analysis of the plasma samples that will be taken on days 1, 7 and 14 of the mifepristone/placebo administration will ensure that the electrolyte levels remain within normal limits (sodium 135–145, potassium 3.5–5.3, chloride 95–105, urea 3.3–6.7, creatinine 40–120, all units micromoles per litre). Blood pressure checks were carried out daily during the acute withdrawal phase (10–14 days) as part of the normal clinical routine, and on day 14 if not measured on that day as part of normal clinical care. In the event of a participant self-discharging from the unit before the course of mifepristone is completed, the mifepristone/placebo treatment will be stopped and the participant will be withdrawn from the trial.

Following recruitment of the first 20 participants the Data Monitoring Committee will carry out a detailed examination of the safely data to ensure that there no problems have arisen with regard to drug safety.

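### The sample-size paragraph calls for 63 per group (126) at an effect size of 0.5 but sets the total at 120, which gives about 78% power and leaves no room for loss

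*Protocol article*

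**What the plan says.** The Sample size section of the protocol article works out per-group numbers "based on a power of 80 % and alpha of 0.05". It gives 25 per group for an effect size of 0.8, and "this increased to 32 for an effect size difference of 0.7 and 63 if the difference was 0.5". It then chooses the smallest of these effects and concludes that the trial "aimed to detect a small to medium effect size of 0.5 and this required 120 subjects participating in the study".

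The Methods/Design part of the Abstract presents 120 as the number to be recruited. Two other sections bear on how many of those recruited will have data:

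- Under Assessment of safety, if a participant self-discharges before completing the course, "the mifepristone/placebo treatment will be stopped and the participant will be withdrawn from the trial".
- Under Primary outcome measures, the two CANTAB sessions fall between days 13 and 20 and between days 21 and 28. The same section says that cognitive testing before treatment would not be valid because of intoxication.

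**The concern.** The per-group figure and the total stand in consecutive sentences and disagree: 2 × 63 = 126, not 120. The text says that 120 was required, not that it is a rounded or approximate figure, so a reader will take 120 as the number that delivers 80% power at 0.5.

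A second consequence follows. A recruitment target below the unadjusted requirement cannot contain any margin for participants who leave before the cognitive outcome is measured, and the protocol itself has a rule that removes some of them.

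At stake is whether the planning statement is accurate. The Cognitive performance section says the trial is meant to supply estimates for future full trials, so a later team could carry forward 120 at 0.5 as an 80% design.

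**Working it through.** **Inputs.** From the Sample size section: effect size 0.5 (SD of 1 on the standardised scale), power 80%, alpha 0.05, 63 per group, total 120. From the Abstract: 120 is the recruitment target. Two points are inferred because the article does not state them: the test is two-sided and allocation is 1:1. Both fit the per-group figures, as the next step shows.

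**Reproducing the plan's per-group figures.** Normal approximation, two-sided: n per group = 2(1.960 + 0.842)² / d².

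| Effect size d | Computed n per group | Stated |
|---|---|---|
| 0.8 | 24.5 | 25 |
| 0.7 | 32.0 (33 if always rounded up) | 32 |
| 0.5 | 62.8 | 63 |

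The per-group figures reproduce, so the formula and the two-sided reading are the right ones.

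**Reproducing the total.** 2 × 63 = 126. The stated 120 is 6 short (6/126 = 4.8%). A one-sided test would need 50 per group, or 100 in total, which matches neither 63 nor 120.

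**Power at the stated total, everyone assessed (60 per group).**

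- Normal approximation: 0.5 × √(60/2) = 2.739; 2.739 − 1.960 = 0.779; Φ(0.779) = 78.2%.
- Two-sample t-test (noncentral t): 77.5%.

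**Effect detectable with 80% power at 60 per group.** Normal: 2.802 × √(2/60) = 0.51. t-test: 0.516.

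**Allowance for loss.** The number recruited (120) is less than the number needed with no loss (126), so the allowance is nil. A participant who leaves before the first CANTAB session has no CANTAB score, because none is taken before treatment.

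**Illustration only.** The document gives no loss rate, so the rates below are assumptions. The powers are for a two-sample t-test on a single CANTAB score at an effect size of 0.5.

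| Assumed loss | Assessed per group | Power |
|---|---|---|
| 10% | 54 | 73% |
| 20% | 48 | 68% |
| 30% | 42 | 62% |

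**The case against.** The best defence is that the gap is trivial. It is 6 participants and about 2 points of power, and the detectable effect moves only from 0.50 to about 0.51 or 0.52. The trial is a proof of concept with no earlier data in its target population, and 0.5 was chosen as a cautious value from published effects running from 0.496 to 0.897. At an effect of 0.7, 60 per group would still give about 97% power. Uncertainty about the true effect matters far more than 126 against 120. Recruitment also closed with 26 plus 1 participants (Trial status), so the correction changes no enrolment decision.

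This stands as an argument about size. It does not make the sentence correct, because the paragraph makes a formal power statement and its own numbers do not yield the total. Low recruitment is a separate matter and does not repair the planning statement.

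Three stronger readings are tempting, and the document does not support them:

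- **That planned power was really 62% to 73%.** Those values depend on assumed losses. The self-discharge rule says what happens to such participants, not how many there will be. An expected loss rate and its justification may stand in the full protocol, which is not shown.
- **That both primary outcomes are equally affected.** The BDI-II is given at screening and every 7 days over the 4 weeks, so an early leaver may already have contributed scores. It is also analysed by repeated measures, to which the two-sample figures do not apply.
- **That 63 is itself wrong because the t-test needs 64.** This is a choice between the normal approximation and the noncentral t, not an error.

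The intention-to-treat analysis listed under Statistical analysis does not answer the point about margin, since it cannot supply cognitive scores that were never collected.

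**Conclusion.** The statement is wrong as written, and the error is minor to moderate. On the plan's own inputs, 80% power at an effect size of 0.5 needs 126 participants with outcome data. The 120 to be recruited give about 78% if all are assessed. This part rests only on the article's figures and on the inferred two-sided test and equal allocation, both of which reproduce the stated 63.

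It also stands that 120 leaves no allowance for loss before CANTAB testing, so power for the cognitive outcome falls below 78% with any such loss. How far below cannot be determined from the document. The finding does not show that the trial needed to enrol more, and it says nothing against the withdrawal rule itself.

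**What to change.** Restate the sentence in the Sample size section, without changing the number to be recruited. For example:

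> 63 per group (126 in total) with outcome data would be required for 80% power at an effect size of 0.5; the 120 to be recruited give about 78% power if all are assessed, and less with any loss before CANTAB testing.

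If the sponsor has an expected loss rate, state it with its basis and the resulting power. The illustrative rates above should not be written into the protocol, because they have no source in it.

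The cost is a change of wording. No procedure, analysis or enrolment target changes. The only downside is that the stated power becomes slightly less favourable.

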### Statistical analysis

The null hypothesis is that there will be no differences in the results from the cognitive testing between participants who received mifepristone and those who received the placebo. Primary data analysis will be by analysis of variance (ANOVA) on the CANTAB results and Beck depression scale scores for mifepristone and placebo groups, with post hoc tests for variables likely to affect these results. Analysis will be carried out both on a per protocol basis and an intention to treat basis.

A repeated measures analysis of variance using treatment type as a between-subject factor (two levels: mifepristone and placebo) and number of times the scale is applied as the within-subjects factor (five levels) will be carried out on the Beck depression scale results. This analysis will examine changes in level of depressive symptoms over the 4 weeks of the study. The analysis on the results from the BDI-II will compare the depressive symptoms prior to mifepristone/placebo with the scores during the four test weeks. This will provide information about whether or not mifepristone alters the progression of such symptoms and enable effect sizes to be calculated for such multiple comparisons in a full trial.

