### Study entry

Prospective participants who are referred for an admission to an alcohol inpatient unit for alcohol detoxification will be identified by the community alcohol teams. If the person is willing to hear more about the research, contact details will be passed to the research team. Written informed consent to complete a preliminary screening appointment will be taken. Eligibility to take part in the research will be checked at a preliminary screening appointment and included administration of the Mini-Mental Sate Examination (MMSE) [39] to screen for any severe cognitive impairment. The Composite International Diagnostic Interview (CIDI) [40] will be administered to demonstrate alcohol dependence of at least 5 years of the patients prior to detoxification according to DSM-IV diagnostic criteria. Plasma alanine aminotransferase (ALT) and creatinine will be measured for indication of liver damage and impaired renal function, respectively. Urine will be tested for evidence of porphyria. If the participant is eligible, consent to take part in the study will be obtained prior to or on admission to the alcohol unit by a clinical member of the research team or a delegated physician. All participants will be advised not to consume grapefruit juice during the trial as this is contraindicated with mifepristone.

At the preliminary screening appointment participants will be asked to complete questionnaires to help establish patterns of alcohol consumption. This includes a measure of the severity of alcohol dependence using the Severity of Alcohol Dependence Questionnaire (SADQ) [41], current craving for alcohol using the Alcohol Urge Questionnaire (AUQ) [42], problems experienced due to alcohol using the Alcohol Problems Questionnaire (APQ) [43], and a retrospective report of the quantity of alcohol consume over the previous 90 days collected using the time-line follow-back (TLFB) [44]. In addition, the Fagerstrom questionnaire [45] will be used to record the amount of smoking and level of nicotine dependence and symptoms of depression will be measured using the Beck Depression Inventory (BDI-II) [46].

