#### Post hoc analysis

Although participants in the two treatment groups will be balanced, potential confounds will be examined as covariates in the post hoc ANCOVA analysis. Covariates will include: severity of withdrawal symptoms (measured by the CIWA-Ar, which primarily examines autonomic symptoms, and the AUQ which measures alcohol craving); presence/absence of depressive symptoms; smoking/non-smoking, chlordiazepoxide dosage; other medication prescribed after detoxification; co-morbid psychiatric disorders other than depression, other medication and age.

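### The primary BDI-II analysis uses the pre-treatment score as a fifth outcome level and not as a covariate, and names no deciding term; baseline adjustment would be a free gain in efficiency

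*Protocol article*

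**What the plan says.** The Statistical analysis section of the protocol article sets a repeated-measures ANOVA for the BDI-II, with treatment as a two-level between-subject factor and "number of times the scale is applied as the within-subjects factor (five levels) will be carried out on the Beck depression scale results". It adds that the analysis "will compare the depressive symptoms prior to mifepristone/placebo with the scores during the four test weeks".

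The Study entry section places one BDI-II at the preliminary screening appointment: "symptoms of depression will be measured using the Beck Depression Inventory (BDI-II"). Under Primary outcome measures the scale is then given weekly over the four trial weeks. One plus four gives the five levels, so the fifth level is the pre-treatment score. This is an inference, but the count and the description of the comparison both support it.

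Covariates appear only under Post hoc analysis. That list includes presence or absence of depressive symptoms, but not the baseline BDI-II score. The Statistical analysis section promises both intention-to-treat and per-protocol analyses.

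**The concern.** A score taken before the first dose cannot carry a treatment effect. Used as a covariate, it removes between-person variation from the later scores. Used as a fifth outcome level, it either pulls the averaged group difference towards zero or serves as the subtrahend of a change score.

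The model also offers three possible tests of treatment: the group main effect, the group-by-occasion interaction, and a pre-versus-post contrast. The section speaks of change over four weeks and of altered progression, which points to the second or third, but it does not say which one decides. The three differ widely in power, so the choice matters and should not be left open until the data are seen.

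At stake are the precision of one of the two primary outcomes and of the effect estimate that this proof-of-concept trial is meant to hand on to a full trial.

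**Working it through.** **The plan's own figure.** The Sample size section works "based on a power of 80 % and alpha of 0.05" and gives "63 if the difference was 0.5" per group. Two-sided, n = 2(1.960 + 0.842)²/0.5² = 62.8, so 63 per group reproduces. The stated total of 120 (60 per arm) gives 78% power at 0.5, not 80%. That calculation rests on CANTAB effect sizes; the document gives no BDI-II power, SD or correlation.

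**Inputs.** From the document: 120 planned, 27 recruited (26 + 1, Trial status), five occasions, alpha 0.05. Assumed: two-sided test, equal allocation, SD 1, equal correlation r between all occasions, no baseline difference, and a constant effect δ over weeks 1 to 4.

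**Formulas** (h = n₁n₂/N, which is 30 for 60 per arm; noncentrality λ):

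- Main effect over five levels: effect 0.8δ, variance (1+4r)/5; λ = h(0.8δ)²/variance, 1 df.
- Interaction: λ = h·0.8δ²/(1−r), 4 and 4(N−2) df.
- Pre-versus-post contrast: effect δ, variance (1+3r)/4 + 1 − 2r, 1 df.
- Baseline-adjusted mean of the four later scores: effect δ, variance (1+3r)/4 − r², 1 df.

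**Numbers at r = 0.5, δ = 0.3, N = 120.** The variances are 0.600 (main effect), 0.625 (contrast) and 0.375 (adjusted). The noncentralities are:

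- main effect: 30 × 0.24²/0.600 = 2.88
- interaction: 30 × 0.8 × 0.09/0.5 = 4.32, spread over 4 df
- contrast: 30 × 0.09/0.625 = 4.32
- adjusted: 30 × 0.09/0.375 = 7.20

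| N, δ, r | Main effect | Interaction | Pre-post contrast | Baseline-adjusted |
|---|---|---|---|---|
| 120, 0.3, 0.5 | 39% | 34% | 54% | 76% |
| 120, 0.3, 0.6 | 35% | 42% | 64% | 80% |
| 120, 0.5, 0.3 | 91% | 63% | 83% | 99% |
| 120, 0.5, 0.5 | 80% | 80% | 93% | 99% |
| 120, 0.5, 0.7 | 70% | 96% | 99% | >99% |
| 27, 0.5, 0.5 | 25% | 21% | 35% | 53% |

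**Variance relative to baseline adjustment** at r = 0.3, 0.5 and 0.7: 1.79, 2.50 and 4.17 times for the main effect (rescaled for its 4/5 size), and 2.27, 1.67 and 1.32 times for the contrast.

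**Where the gain fades.** These are simulations with 60 per arm and 1,500 runs each, with the mixed model given its true covariance, which flatters it slightly.

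- Baseline correlation 0.3, later scores 0.6 among themselves, constant effect 0.5: 78%, 68%, 74% and 93%, in the order of the table.
- Same correlations, effect rising linearly to 0.5 at week 4: the interaction has 60% and the mixed model 59%, so there is no gain over the interaction.

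**Missing visits.** If the ANOVA were run in its classical form, on participants with all five scores, an assumed 20% dropout by week 4 (δ = 0.5, r = 0.5) would leave 72%, 68% and 87%, against 99% for a mixed model using every available visit.

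**The case against.** The strongest reply is that the planned test is valid under randomisation and that, at the one effect size the document targets, it does well enough. That stands: with 120 participants, δ = 0.5 and r = 0.5, all three candidate tests reach about 80% or more. The weak results come at smaller effects or smaller numbers.

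Three stronger readings are tempting, and the document does not support them.

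- A reader might infer that the plan dilutes the treatment effect outright. The 4/5 factor applies only to the between-group main effect. The section's wording leans towards change over time, where the fault is inefficiency and an unnamed deciding term.
- A reader might infer that anyone with a missed week is excluded, in breach of intention to treat. That is how a classical repeated-measures ANOVA behaves, but the article does not state it, and a full protocol or analysis plan not shown may deal with missing data. Loss rates are also assumptions: the article gives none and describes only withdrawal after self-discharge (Assessment of safety).
- A reader might infer far more power in general. That depends on correlation and effect shape, which the document does not give. A weakly correlated baseline is plausible, because the screening BDI-II precedes detoxification and the Background expects most depressive symptoms to resolve spontaneously.

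Against this, even the most favourable reading of the text, the pre-versus-post contrast, has lower power than baseline adjustment in every row of the table.

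**Conclusion.** The point holds as one of efficiency and specification. The primary BDI-II model spends the pre-treatment score as an outcome level, does not adjust for it, and leaves the deciding term unnamed.

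With a constant effect, compound symmetry and a correlation around 0.5, baseline adjustment lifts power at 0.3 SD from between 34% and 54% to 76%. The gain is large against the main effect at moderate or high correlation, small against the contrast at high correlation, and about nil against the interaction when the effect builds slowly and the baseline correlates weakly.

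The planned analysis is not an invalid test. Nor does the change rescue the trial: with 27 participants it gives about 53% power at 0.5 SD, against 21% to 35% for the planned alternatives. Loss of participants with an incomplete series is a conditional risk that sits poorly with the promised intention-to-treat analysis; it is not an established fault.

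**What to change.** Before unblinding, replace the five-level ANOVA with a mixed model on the four post-randomisation BDI-II scores, with treatment, week, treatment-by-week and the screening BDI-II as covariate, using all available visits. Name one primary contrast: the treatment difference averaged over weeks 1 to 4.

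With 27 recruited, use a simple covariance structure such as compound symmetry and few further covariates. An unstructured covariance with SADQ, age and five sites would be too heavy for this number.

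The cost is a change of wording in the analysis section or plan. No new data are needed, because the screening BDI-II is already collected.

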#### Cognitive performance

Reliable estimates of potential effects and variances will be obtained which will enable such repeated analysis in future, full clinical, trials (repeated measures analyses will not possible in this initial Proof of Concept study, as there will be insufficient information on between and within group variances).

#### Post hoc analysis

Although participants in the two treatment groups will be balanced, potential confounds will be examined as covariates in the post hoc ANCOVA analysis. Covariates will include: severity of withdrawal symptoms (measured by the CIWA-Ar, which primarily examines autonomic symptoms, and the AUQ which measures alcohol craving); presence/absence of depressive symptoms; smoking/non-smoking, chlordiazepoxide dosage; other medication prescribed after detoxification; co-morbid psychiatric disorders other than depression, other medication and age.

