### Randomisation and blinding

Randomisation will be carried out after consent is gained for participation in the main trial for those participants who are eligible. A remote randomisation procedure will be used through an online system based at the King’s Clinical Trials Unit at the Institute of Psychiatry, King’s College London. This involves allocation of unique identification numbers for each participant. The minimisation method will be used for the allocation that involves stratification by severity of alcohol dependence (SADQ score of over 40 or under 40), site and age (18 to 29, 30 to 39, 40 to 49 or 50 to 60). These variables are known to be potential confounders with the observed outcome and are collected at preliminary screening.

As this is a multi-centre study and allocation is blind, those conducting the randomisation will not be in a position to subvert the allocation sequence. The blister packs contain 7 tablets and will be supplied in individual cartons with a label on the front face of the carton bearing a unique kit identification number (Kit ID). The Kit ID is pre-printed on the label by the packaging company. Participants will be allocated Kit IDs according to the remote randomisation procedure. Each carton sent to the Pharmacy by the manufacturing company will be accompanied by an individual sealed code-break envelope in case of emergency unblinding. Participants, researchers and ward staff will be blind to which treatment each patient is given.

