### Primary outcome measures

Cognitive ability will be measured using the CANTAB. The CANTAB has been used extensively in research and previous studies have been published that have used the CANTAB test battery in patients with depression and patients with alcohol dependence [47–52]. The CANTAB testing will compare mifepristone and placebo groups concurrently. Cognitive function measurement prior to mifepristone/placebo would not be valid owing to intoxication. A pretest will be carried out on the day before the first CANTAB testing, composed of the Motor Screening task and the Reaction time task. These two tests are designed to assess basic motor and visual skills and determine whether participants are capable of being tested on CANTAB. The CANTAB tests that will be used at the two cognition testing times (between days 13 and 20 and 21 and 28) are: visuospatial ability by Reaction Time, Pattern Recognition, Matching to Sample Visual Search, Spatial Recognition memory and Paired Associates tasks; sustained attention by the Rapid Visual Processing task; and executive function by Intra- and Extra-Dimensional Shifting, Spatial Working Memory and Stockings of Cambridge tasks.

The above CANTAB test times will enable examination of cognitive testing administration of chlordiazepoxide ceases, as benzodiazepines are well established to affect memory and learning. Urine samples taken on the day of CANTAB testing will be screened for the presence of residual chlordiazepoxide or its active metabolites, which may affect cognitive performance [53].

The BDI-II [46] will be used to record symptoms of depression throughout the trial. It will be administered at every 7 days during the 4 weeks the participant is in the trial and at 3, 6 and 12 months follow-up from cessation of drinking. The BDI-II will be administered on the day of the CANTAB testing so that the results can be used as a variable in the measure of cognitive function.

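### The post hoc ANCOVA treats as confounds several variables that arise after randomisation and that the drug may change, so its estimates would not measure the total effect of assignment

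*Protocol article*

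**What the plan says.** The Statistical analysis section makes the primary analysis an ANOVA of the CANTAB and BDI-II results by treatment group and names no covariates. It adds post hoc tests for variables thought likely to influence the results. The Post hoc analysis section then states that "potential confounds will be examined as covariates in the post hoc ANCOVA analysis". Its list opens with withdrawal severity (CIWA-Ar and AUQ) and continues with "presence/absence of depressive symptoms; smoking/non-smoking, chlordiazepoxide dosage; other medication prescribed after detoxification", other psychiatric co-morbidity, other medication and age.

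Primary outcome measures schedules the BDI-II on the CANTAB days "so that the results can be used as a variable in the measure of cognitive function".

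Randomisation and blinding describes minimisation on SADQ (above or below 40), site and age band, and says of these factors: "These variables are known to be potential confounders with the observed outcome and are collected at preliminary screening". Of the three, only age appears in the covariate list.

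**The concern.** Randomisation makes the arms comparable at entry. A variable measured later is not a confounder of the treatment comparison; it may be a consequence of treatment. Adjusting for it does two things. It removes whatever part of the effect runs through that variable. If the variable shares an unmeasured cause with the outcome, it also opens a non-causal path between treatment and outcome (collider bias).

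The article itself gives reasons to expect the drug to act on these variables. The Objectives compare the arms on withdrawal severity and craving. The Background cites fewer withdrawal signs in animals and less cue craving in a clinical trial. It also says that mood and cognition are related in an uncertain direction, with glucocorticoids implicated in both. At stake is an adjusted result presented as the comparison with confounding removed, when it answers a different question. The trial's third hypothesis is causal, so the distinction matters.

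**Working it through.** **1. Timing of each listed covariate.** According to the Abstract, randomisation is on admission.

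| Covariate | When measured, per the article | Pre-randomisation value? |
|---|---|---|
| CIWA-Ar | daily from 24 h after drinking stops | none among the screening measures |
| Chlordiazepoxide dosage | as needed, usually the first 7 to 10 days, alongside trial drug | not possible |
| Medication after detoxification | later still | not possible |
| Depressive symptoms (BDI-II) | screening, weekly, and CANTAB days (between days 13 and 28) | yes, at screening |
| AUQ | screening and every 7 days | yes, at screening |
| Smoking, age | screening | yes |

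The first three cannot be read as baseline covariates. For BDI-II and AUQ the list does not say which measurement is meant, but the Primary outcome measures wording points to the test-day BDI-II.

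**2. The plan's own sample size figures.** Inputs are "based on a power of 80 % and alpha of 0.05" (two-sided and 1:1 assumed), and n per group = 2(1.96 + 0.8416)²/d² = 15.70/d².
- d = 0.8: 24.53, stated as "25 subjects per group would be required".
- d = 0.7: 32.04, stated as 32.
- d = 0.5: 62.79, stated as 63.

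The figures reproduce to within rounding. At the planned 120 (60 per arm), power for d = 0.5 is Φ(0.5/√(2/60) − 1.96) = Φ(0.779) = 78.2%, or 77.5% by the noncentral t. This is the baseline for what follows.

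**3. One mediator (assumed inputs).** Let a be the drug's effect on the covariate in SD, and b the covariate's slope on the outcome. Then adjusted effect = 0.50 − a·b, with SE = √[(1 − b²)(1 + a²/4)] × √(2/60).

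| a | b | Adjusted effect (SD) | Share removed | Power of adjusted test, 60 per arm |
|---|---|---|---|---|
| 0.2 | 0.2 | 0.46 | 8% | 73% |
| 0.3 | 0.3 | 0.41 | 18% | 64% |
| 0.5 | 0.5 | 0.25 | 50% | 34% |

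**4. Collider bias alone (assumed inputs).** Take k = 4 covariates, no drug effect on the outcome, and an unmeasured cause with loading c = 0.5 on each covariate and on the outcome. Bias = −k·a·c²/(1 + (k − 1)c²) = −0.571a, which is −0.11, −0.17 and −0.29 SD for a = 0.2, 0.3 and 0.5. Simulation (60 per arm, 4,000 runs) gave −0.109, −0.173 and −0.286, with type I error of 9%, 17% and 33% instead of 5%.

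**5. Minimisation factors.** SADQ (two levels) and five sites cost q = 1 + 4 = 5 degrees of freedom. Adjustment breaks even when (1 − R²)(N − 3)/(N − 3 − q) = 1, so R² = q/(N − 3): 5/117 = 4.3% at N = 120, and 5/24 = 20.8% at the 26 + 1 = 27 reported under Trial status. Noncentral-t power for d = 0.5:
- N = 120: 77.5% unadjusted; 75.7%, 77.8%, 80.0% and 84.4% adjusted at R² = 0, 0.05, 0.10 and 0.20.
- N = 27: 23.9% unadjusted; 19.6%, 21.3%, 23.4% and 26.0% adjusted at R² = 0, 0.10, 0.20 and 0.30.

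A linear age term makes q = 6 and moves break-even to 6/117 = 5.1% and 6/24 = 25%. Pooling sites lowers it.

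**The case against.** A reader might infer that the trial's main result is biased. The article does not support that. The primary ANOVA is unadjusted, the ANCOVA is labelled post hoc, covariates are only to be examined, and nothing lets the adjusted result replace the primary one. This part of the objection stands in full.

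A reader might also take every listed item to be post-randomisation. That is not supported either. AUQ, BDI-II and smoking are recorded at screening, and those values are legitimate covariates. The objection does not rescue CIWA-Ar, chlordiazepoxide dosage or later medication, or the planned use of test-day BDI-II.

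Benzodiazepines impair memory, and the article plans urine screening for residual drug on test days, so looking at dose has a stated purpose. That justifies an exploratory analysis. It does not make dose a confounder.

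The illustrative sizes rest on assumed a, b and c, and treat the covariates as continuous, whereas the list has depressive symptoms as present or absent. At the low end only 8% of the effect is lost.

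Finally, the absence of SADQ and site could be read as an error in the primary model, or as precision given up for nothing. The covariate list is open-ended, the full analysis plan is not shown, and the gain is not free. This half is a suggestion only.

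**Conclusion.** The point holds for the adjusted analysis alone. As worded, the ANCOVA conditions on at least three variables that can exist only after randomisation and, under Primary outcome measures, on a co-primary outcome measured on the test day. Its estimates would not be the total effect of assignment to mifepristone. With one mediator and a and b each between 0.2 and 0.5, a 0.50 SD effect shrinks to between 0.46 and 0.25 SD. With a shared unmeasured cause the error can also produce a spurious difference. The article supplies none of these inputs, so the actual size and direction are unknown.

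Including the minimisation factors is a secondary matter. It gains power at 120 only if they explain more than about 4 to 5% of the variance, and at 27 only above about 20%.

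**What to change.** 1. Limit the adjusted analysis to values fixed before randomisation: SADQ, age, site, screening BDI-II, screening AUQ and smoking status. State that the screening measurement is the one used.
2. Take CIWA-Ar, on-trial AUQ, test-day BDI-II, chlordiazepoxide dosage and later medication out of the list of confounds. If they are of interest, report them separately as exploratory mediation, with the unmeasured-common-cause assumption stated.
3. As an optional improvement, put SADQ, age and site (pooled where small) in the models for both primary outcomes, decided before unblinding.

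Items 1 and 2 need only a change of wording, because all the replacement variables are already collected. Item 3 costs about 5 degrees of freedom for SADQ and site and a little more for age. At the 27 recruited it may reduce power slightly, so site pooling matters and the choice should be recorded with its reason.
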